### Study objective

This study is designed to evaluate the analgesic efficacy of 5 consecutive tDCS sessions to the primary motor cortex in patients with cancer pain in the palliative care setting.

The primary endpoint is the score of the numerical rating scale (NRS), which measures pain intensity on a scale from 0 to 10 [36]. The mean of 3 NRS scores recorded during the day (morning, midday and evening) will be used. The primary endpoint for analysis will be the mean variation of the pain NRS between the baseline assessment (D0) and the D8 assessment.

The secondary objectives will be to evaluate:Immediate impact of each tDCS session on pain intensity.Response rate at the end of treatment.Residual analgesic effect.Effects of TDCS on the other main symptoms likely to impair quality of life.Analgesic consumption on D0 and D8.

Secondary endpoints will be:Pain NRS score, MQS (Medication Quantification Scale [37]), including evaluation of opioid consumption expressed in oral morphine equivalent per day on D0 and D8.Pain NRS scores, recorded before and after each session.Efficacy of treatment, defined by a ≥ 20% reduction of the mean NRS score between D0 and D8 (IMMPACT recommendation in chronic pain [38]).Mean NRS score on D14 and D21 in the 2 arms.Completion of the following questionnaires and scales on D0 and D8:. BPI (Brief Pain Inventory, short form [39]).. ESAS (Edmonton Symptom Assessment System) [40].. HADS (Hospital Anxiety and Depression Scale) [41].. STAI-Y (State-Trait Anxiety Inventory (Form Y) [42]).Analgesic consumption assessed by MQS on D0 and D8.

Analysis of repeated measurements of quantitative secondary endpoints (NRS, BPI, ESAS, HADS, STAI-Y and MQS) will be based on the mean variations of the endpoint between the baseline assessment (D0) and the D21 assessment.

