**Method/design:**

This article describes the protocol of a bicentre, randomized, parallel-arm, sham-controlled clinical trial evaluating tDCS in the treatment of palliative care patients with refractory cancer pain. Seventy patients between the ages of 18 and 80 years experiencing refractory pain with a pain score of 4/10 on a numerical rating scale (NRS) ranging from 0 to 10 will be enrolled in this trial. The main exclusion criteria are patients unable to fill in the various rating scales and life expectancy less than 3 weeks. Treatment consists of 5 consecutive tDCS sessions targeting the motor cortex (one daily session for 5 days) on the contralateral side to the pain. After randomization (1:1 ratio), 35 patients will receive active stimulation and 35 patients will receive sham stimulation. The primary endpoint is the NRS score and the primary objective is a significant improvement of this score between the baseline score recorded between D-3 and D-1 and the score recorded 4 days after stopping treatment (D8). The secondary objectives are to evaluate whether this improvement is maintained 16 days after stopping treatment (D21) and whether the following scores are improved on D14 and D21: Brief Pain Inventory, Edmonton Symptom Assessment System, Hospital Anxiety and Depression scale, State-Trait Anxiety Inventory and Medication Quantification Scale.

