### Benefits and risks

At the individual level, pain intensity is expected to decrease by the 2nd or 3rd tDCS session, with a more marked improvement after the 5th session. This improvement is expected to last at least 4 days (D8) and up to 16 days (D21) [15, 18]. It should be possible to markedly decrease analgesic drug treatment during this period, which should result in less drowsiness and improved activities of daily living. An improvement of sleep, tiredness and mood can also be expected. The patient may be able to return home during the week after the end of treatment with a markedly reduced workload for the patient’s caregivers.

Side effects are recorded in the electronic observation booklet after each tDCS session (D0, D1, D2, D3, D4) and during the 3 subsequent evaluations (D8, D14 and D21). Side effects [32] such as headaches or vomiting that are repeated or even worsen with each tDCS may force the patient to stop the treatment if they are prolonged or poorly tolerated. The most frequent side effect is a bad tolerance of the stimulation itself. The patient may have a sensation of electrical discharge or burning sensations at the positioning of electrodes*,* especially in the event of excessive stimulation (> 2 mA) delivered by excessively small electrodes (< 20 × 20 mm) [32]. At the most, there may be a real burn on the scalp in contact with the electrode. Initially, the proper impregnation of the sponge electrodes by the saline solution will be checked and if the phenomenon continues, the stimulation intensity will be decreaed to 1.5 mA. In the event that these adverse effects persist, the treatment will be stopped. The risk of inducing seizures is almost non-existent, but it is recommended to avoid tDCS in patients with seizures not controlled by medical treatment.

A significant collective benefit could be observed, and tDCS could markedly decrease the length of hospital stay of these patients and their analgesic drug consumption and should therefore have a significant health economics impact. In parallel, the patient’s and caregivers’ quality of life could be significantly improved. In the longer term, continuation of tDCS at home would require a new organization. The development of remote treatment techniques must also be considered [24].

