**Fig. 1 Fig1:**
[figure not shown]
Study plan: the study will last 24 days (D-3 to D21) including a 3-day inclusion period (D-3-D0), a 5-day treatment period (D0-D4) and a 16-day follow-up period after stopping treatment (D8, D14, D21). Treatment consists of a daily tDCS session on 5 consecutive days. Patients will be randomized to 2 arms (1:1 ratio): active tDCS and sham tDCS. Patients and investigators will be blinded to the results of randomization (double-blind). The primary objective will be a significant reduction of pain evaluated by a numerical rating scale (NRS) from 0 to 10 between the baseline score recorded between D-3 and D0 and the score recorded 4 days after stopping treatment (D8)

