#### Inclusion visit (visit 1) (D0)

Recording of NRS scores for 48 hours (D-3 to D-1) allowing inclusion of the patient. Recording of clinical parameters such as age, sex, weight, height, etc., medical history, previous and concomitant treatments, vital signs. Baseline assessment: NRS, BPI, ESAS, HADS, STAI-Y and MQS (see secondary endpoints). Randomization (by centre, 1:1 ratio). Study personnel (physician and nurses specialized in pain management) will be blinded to the results of randomization.

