#### Treatment with active or sham tDCS (D0-D4)

Study personnel (physician or trained nurse), but not the patient, will be informed about the results of randomization. tDCS will be delivered daily for 5 consecutive days. The NRS will be scored 3 times a day on these 5 days from Monday to Friday.

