### Randomization

Centralized randomization will be performed on D0 after verification of the inclusion criteria. Randomization will be performed under double-blind conditions and will be stratified according to the mean baseline pain intensity (4–6 or 7) over the last 48 hours before inclusion and according to centre.

Patients will be randomized to receive either active tDCS or sham tDCS for the 5 treatment days defined by the protocol. The randomization ratio will be 1:1. Randomization will be stratified by centre by means of the Ennov Clinical electronic CRF (https://fr.ennov.com/getions-essais-cliniques/) by logging onto the website: https://nantes-lrsy.hugo-online.fr/CSOnline/ after obtaining the patient’s informed consent on D0. The inclusion number and randomization arm will be automatically allocated at the time of randomization. A confirmation e-mail will be sent to the person who performed randomization and to all other people concerned.

Randomization lists will be established by a Nantes university hospital research promotion department statistician.

A patient registered in the trial, to whom treatment has been allocated and documented, will be considered to be randomized. A patient cannot be included, evaluated or randomized in the trial more than once.

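### The pain baseline is stated inconsistently, and one version, the D0 day mean, can include scores taken after the first tDCS session

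*Protocol article*

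**What the plan says.** Three places in the protocol article define the starting point of the primary NRS comparison.

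- Abstract, Method/design: "the baseline score recorded between D-3 and D-1 and the score recorded 4 days after stopping treatment (D8").
- Fig. 1 legend: "the baseline score recorded between D-3 and D0 and the score recorded 4 days after stopping treatment (D8").
- Study objective: "The primary endpoint for analysis will be the mean variation of the pain NRS between the baseline assessment (D0) and the D8 assessment".

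On how a day's score is formed, Study objective says: "The mean of 3 NRS scores recorded during the day (morning, midday and evening) will be used".

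D0 is also a treatment day. Benefits and risks lists side-effect recording "after each tDCS session (D0, D1, D2, D3, D4"), the treatment section says "The NRS will be scored 3 times a day on these 5 days from Monday to Friday", and the Randomization section says "Centralized randomization will be performed on D0 after verification of the inclusion criteria". Session 1 therefore falls on D0, after randomization. Its clock time is not given.

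The inclusion visit (D0) section covers the weekend scores, "Recording of NRS scores for 48 hours (D-3 to D-1) allowing inclusion of the patient", and then lists a baseline assessment that includes the NRS, ahead of randomization. Table 1 has a D0 column with NRS and randomization but no tDCS, and a separate D0-D4 column with tDCS and NRS.

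The Analysis of the primary endpoint section compares the mean D8 score between arms in a mixed linear model that accounts for the stratification factors. It mentions no subtraction of a baseline.

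**The concern.** A baseline should be measured wholly before treatment. If the D0 baseline is the mean of that day's three scores, and one or two of them follow session 1, any same-day effect lowers the baseline in the active arm only. Change from baseline to D8 then understates the benefit.

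The protocol does not rule out such an effect. The immediate impact of each session is a secondary objective, and General study methodology allows analgesic doses to come down from the first day of tDCS, depending on its effect. Scores later on D0 may therefore reflect both the stimulation and a change in analgesics made after randomization.

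The change endpoint in Study objective is exposed. So are the responder endpoint (a reduction of at least 20% from D0 to D8) and the changes from D0 to D21. Apart from any bias, conflicting definitions leave it unclear which scores make up the primary endpoint, and that is for the protocol to fix.

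**Working it through.** **1. The plan's own figure.** Inputs from Statistical analysis: difference 2 points, SD 2.8, power 80%, alpha 5%. Sidedness is not stated, and two-sided reproduces the figure. The two-sample t-test needs 31.76, so 32 per arm, which is the stated number. Power is 80.3% at 32 per arm and 83.8% at the planned 35 per arm. The sample size is not in error.

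**2. Which scores can form the baseline.** The screening visit is on a Friday (D-3). NRS is scored three times a day on Saturday and Sunday (D-2 and D-1), giving six scores, and inclusion is decided on Monday (D0). Three readings of the D0 baseline fit the text:

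- the weekend mean, collected at the D0 visit: wholly before treatment;
- an NRS taken at the D0 visit before randomization: also before treatment, but not a three-score day mean;
- the three-score mean for D0: the literal result of the day-mean rule in Study objective, and likely to include at least one score after session 1 unless that session follows the evening score.

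**3. Size under the third reading, if change is analysed.** Let e be the net between-arm effect on D0 scores taken after session 1, and k the number of the three D0 scores taken after it.

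Contrast in (D8 minus D0 day mean) = 2 − e × k/3

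The documents give neither e nor k. I assume e from 0 to 1.0 point and k of 1 or 2, and hold the SD at 2.8. Power is from the two-sided t-test with 35 per arm.

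| e (assumed) | k | Loss e × k/3 | Contrast | Power |
|---|---|---|---|---|
| 0 | 1 or 2 | 0 | 2.00 | 84% |
| 0.25 | 1 | 0.08 | 1.92 | 81% |
| 0.25 | 2 | 0.17 | 1.83 | 77% |
| 0.5 | 1 | 0.17 | 1.83 | 77% |
| 0.5 | 2 | 0.33 | 1.67 | 69% |
| 1.0 | 1 | 0.33 | 1.67 | 69% |
| 1.0 | 2 | 0.67 | 1.33 | 50% |

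**4. Responder endpoint.** A 20% reduction requires a D8 score of at most 0.8 × baseline. If the active-arm baseline is lowered by e × k/3, the D8 score needed to count as a response falls by 0.8 × e × k/3. Over the same range that is 0 to 0.8 × 0.67 = 0.53 point, in the active arm only.

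**5. D8-score comparison.** A between-arm comparison of D8 means does not use D0 scores. The pain stratum in the model is the mean over the 48 hours before inclusion, which is before treatment. The contrast stays at 2 points whatever was recorded on D0.

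**The case against.** A reader might infer that the primary baseline definitely contains post-session scores and that the primary test therefore loses part of its effect. The documents do not support that much.

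- No session time is stated. The inclusion visit lists the baseline NRS ahead of randomization, and Table 1 separates D0 from D0-D4. A clean D0 baseline is a fair reading.
- The abstract and the Fig. 1 legend may describe the same 48 hours. General study methodology labels its 48-hour period of stable medication D-3, D0, while the inclusion visit labels its 48 hours of scores D-3 to D-1. Part of the conflict may be loose labelling.
- The primary analysis section compares D8 scores and subtracts nothing.
- Benefits and risks expects pain to fall by the second or third session, so little may happen after the first.
- Any dilution is towards no difference and would not create a false positive.

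All of this stands, and it makes the loss conditional. It does not remove the inconsistency. A single pre-randomization score is not the day mean that Study objective prescribes, so that reading adds another candidate baseline and settles nothing. Study objective also states the primary endpoint as change from D0, which the D8-score analysis does not match. The responder and D0-to-D21 endpoints need a D0 baseline under any reading.

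**Conclusion.** The point holds in conditional form. The baseline labels conflict and must be reconciled, and the literal D0 day mean can include scores taken after session 1.

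The loss is 0 to 0.67 point of the planned 2, with power at 35 per arm from 84% down to 50%. It arises only if change from a D0 day mean is what is analysed and session 1 already has an effect. The bottom of the range needs a 1.0-point first-session effect and two of three scores after the session together, and the protocol's own expectation about onset points to the small end. With no first-session effect nothing is lost. The values of e and k, the constant SD and the two-sided test are assumptions.

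If the D8-score comparison is the primary test as written, that test is unaffected. The change, responder and D0-to-D21 endpoints keep the risk.

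**What to change.** - In the abstract, Study objective, the Fig. 1 legend and Statistical analysis, define the pain baseline once, as the mean of the six NRS scores from Saturday and Sunday (D-2 and D-1). These scores already serve eligibility and stratification.
- Use this baseline for the change, responder and later NRS comparisons. Exclude from any baseline every score taken at or after the first session.
- Reconcile the primary endpoint in Study objective (change) with the primary analysis (D8 score), for example by comparing D8 NRS between arms adjusted for this baseline.

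The cost is wording only, since the scores are already collected and patients do nothing extra. One small downside is that the same scores decide eligibility, so regression to the mean will enter the change within each arm. It does so equally in both arms and does not bias the comparison between them.

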### Statistical analysis

Statistical justification of the sample size: a 2-point improvement of the numerical rating scale is considered to be clinically relevant [51], which is supported by data from the study conducted by Cheung [55] on the efficacy of ketamine in a population of patients in palliative care setting (see “Clinical Parameters”).

As this is the first protocol dedicated to the treatment of painful patients in a palliative care setting with tDCS, we did not find any evidence in the literature that could help us justify the number of needed patients for the evaluation of the other clinical parameters, apart from the NRS.

On the basis of these hypotheses:A mean NRS difference of 2 points between the active tDCS arm and the sham tDCS arm,Standard deviation of 2.8,Power of 80%.Alpha risk of 5%,

32 patients per arm would be necessary, i.e. a total of 64 patients. In order to ensure sufficient power, an additional 10% of patients will be included in the study, i.e. a total of 70 patients.

The study will therefore include 70 patients: 35 in the tDCS arm and 35 in the sham tDCS arm.

The variables measured on inclusion will be described for all patients and in each of the two arms by number and percentage for each modality for qualitative variables and by minimum, maximum, mean, standard deviation and quartiles for quantitative variables. The primary efficacy population will be a modified intention-to treat (mITT) population, comprising all randomized patients who have received at least one tDCS session (active or sham) and who were evaluated on D0 (baseline) and on D8.

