#### Analysis of secondary endpoints

The mean NRS score on D8 will be compared between the active tDCS arm and the sham tDCS arm using a mixed linear model in order to take stratification factors into account. This analysis will also be adjusted for analgesic consumption based on the MQS score.

The immediate efficacy of tDCS on pain intensity will be compared between the two arms using a mixed linear model with the pre- and post-tDCS difference of the NRS score as the variable to be explained. This model will take repeated measures per patient into account.

The response rate will be compared between the two arms by a mixed logistic model in order to take stratification factors into account.

The residual analgesic effect on D14 and D21 will be studied using a mixed linear model in order to take stratification factors into account. This analysis will also be adjusted for analgesic consumption.

The course of quality of life assessed by the BPI, ESAS, HADS and STAI-Y between D0 and D7 will be compared between the two arms by a mixed linear model in order to take stratification factors into account.

Analgesic consumption, evaluated by the MQS questionnaire, will be compared between the two arms using a mixed linear model.

Complementary analysis of the primary efficacy endpoint could be conducted on a per protocol population including all patients of the mITT population not presenting any major protocol violations. These major violations will be defined in the analysis plan before locking the database.

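### BPI, ESAS, HADS, STAI-Y and MQS are compared as change from D0, and the article does not name each scale's own D0 score as a covariate; naming it would gain precision at almost no cost

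*Protocol article*

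**What the plan says.** **Outcome form.** The Study objective section states that, for NRS, BPI, ESAS, HADS, STAI-Y and MQS, the analysis of repeated measurements "will be based on the mean variations of the endpoint between the baseline assessment (D0) and the D21 assessment".

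**Model for the four questionnaires.** Under Analysis of secondary endpoints, the course of BPI, ESAS, HADS and STAI-Y "will be compared between the two arms by a mixed linear model in order to take stratification factors into account".

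**Model for MQS.** The same section says: "Analgesic consumption, evaluated by the MQS questionnaire, will be compared between the two arms using a mixed linear model". No adjustment is attached to that sentence.

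**Strata.** Under Randomization, allocation is "stratified according to the mean baseline pain intensity (4–6 or 7) over the last 48 hours before inclusion and according to centre".

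**A covariate named elsewhere.** For the secondary NRS comparison at D8 the article adds: "This analysis will also be adjusted for analgesic consumption based on the MQS score". A similar adjustment is stated for NRS at D14 and D21.

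**Data available.** The Inclusion visit (D0) section and Table 1 show that all five scales are scored at D0.

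**The concern.** A change score subtracts the D0 value in full, which fixes the slope on baseline at 1. When D0 and follow-up correlate less than perfectly and have similar spread, the best slope is below 1. The subtraction then over-corrects: an arm that happens to start worse tends to show more improvement through regression to the mean, and the contrast is noisier than it need be.

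The named stratification factors remedy this only in part. They carry centre and a coarse category of baseline pain. They say little about a patient's D0 anxiety, depression or analgesic load.

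These scales support the article's hopes for better quality of life and lower analgesic consumption. The sample size was set on the NRS alone, and the Statistical analysis section says no evidence was found for sizing the other parameters. Precision that costs nothing is therefore worth having here.

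**Working it through.** **The article's own figure.** The only sample size it computes is for the primary NRS comparison, from "A mean NRS difference of 2 points between the active tDCS arm and the sham tDCS arm", SD 2.8, power 80% and alpha 5% (taken as two-sided).

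- Normal approximation: n per arm = 2 × (1.96 + 0.84)² × (2.8/2)² ≈ 31.
- t-test version: 31.76, so 32 per arm and 64 in total, as stated.
- 64 × 1.10 = 70.4, stated as 70.

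The figure reproduces. It gives no effect size, SD or correlation for the secondary scales, so what follows uses an assumed range of rho.

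**Inputs for the check.** 32 patients per arm (from the article); equal SD at D0 and follow-up, set to 1 (assumed); rho from 0.3 to 0.9 (assumed).

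**Formulas.**

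- Variance of a change score: 2(1 − rho).
- Variance after adjustment for D0: 1 − rho².
- Adjusted over change: (1 − rho²) / [2(1 − rho)] = (1 + rho)/2, so the variance cut is (1 − rho)/2.
- Shift of the change-score estimate for a D0 difference d between arms: (rho − 1)d.

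| rho | Change variance | Adjusted variance | Variance cut | SE of change contrast larger by | Power of change score where adjusted has 80% | Shift for D0 difference d |
|---|---|---|---|---|---|---|
| 0.3 | 1.40 | 0.91 | 35% | 24% | 62% | −0.7d |
| 0.5 | 1.00 | 0.75 | 25% | 15% | 68% | −0.5d |
| 0.7 | 0.60 | 0.51 | 15% | 8% | 73% | −0.3d |
| 0.8 | 0.40 | 0.36 | 10% | 5% | 76% | −0.2d |
| 0.9 | 0.20 | 0.19 | 5% | 3% | 78% | −0.1d |

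The 80% in the power column is a reference level for comparison. The article claims no power for these scales.

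**Size of a chance imbalance.** With 32 per arm the standard error of a D0 difference is √(2/32) = 0.25 SD. A D0 difference of that size shifts the change-score estimate by 0.7 × 0.25 = 0.175 SD at rho 0.3, 0.125 SD at 0.5, 0.075 SD at 0.7 and 0.025 SD at 0.9.

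**Simulation.** With 64 patients, no treatment effect and 10,000 replicates, the variance ratio of change to adjusted was 1.52, 1.31 and 1.16 at rho 0.3, 0.5 and 0.7. The formula 2/(1 + rho) gives 1.54, 1.33 and 1.18. Both estimators averaged about zero, so neither is biased over randomisation.

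**The case against.** The strongest reply is that the omission is read from silence. A reader might infer that the scales will be analysed as raw changes with no covariate at all. The article does not say that: it never excludes a D0 covariate, and for the four questionnaires it does name the stratification factors. A change outcome is also compatible with baseline adjustment, because change with D0 in the model gives the same treatment estimate as follow-up with D0 in the model. Covariate lists are often left to an analysis plan, and none is shown here. This stands, and it limits the point to what the article names. However, the article states adjustments endpoint by endpoint and adds MQS for some NRS analyses, so its text can fairly be taken as describing the intended models.

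A second reply is that a mixed model of the course from D0 may treat D0 as a response. With a common D0 mean for both arms, that model does adjust for baseline. With free arm means at D0 and complete data, it returns the change-score contrast. The article does not say which is meant.

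A third reply concerns bias. A reader might infer that chance imbalance biases the comparison. It does not: the shift is conditional on the imbalance that occurs and averages to zero over randomisation.

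Finally, the pain stratum already adjusts part of the baseline for BPI and for the ESAS pain item, so the tabulated gains overstate the benefit for those scores. At rho 0.9 the gain is slight for any scale.

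**Conclusion.** The point holds as a low-cost improvement to secondary analyses. It is not an error that invalidates them. The article fixes change from D0 as the outcome and names only centre and the pain category for BPI, ESAS, HADS and STAI-Y, and nothing for MQS. Analysed that way, the estimates are valid but looser than the D0 data allow, and they carry a conditional dependence on chance imbalance.

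The variance saved runs from about 35% at rho 0.3 to about 5% at rho 0.9, under equal variances and before any credit for the pain stratum. Neither rho nor the equality of variances can be checked from the article, so the gain for any one scale is unknown. The documents do not support the stronger readings that a D0 covariate is excluded or that the planned comparison is biased.

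**What to change.** In Study objective and in Analysis of secondary endpoints, state that each model for BPI, ESAS, HADS, STAI-Y and MQS includes the patient's own D0 score on that scale as a continuous fixed covariate, alongside the stratification factors. For the MQS outcome this is the D0 MQS. The outcome may stay as change or become the follow-up score; the treatment estimate is the same.

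The cost is one sentence and one degree of freedom per model, with no new data and no more patients.

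The same passages should also settle the analysed time point. Study objective refers to D8 and D21, while the questionnaire model runs to D7, which is not a visit in Table 1. That is a separate matter, and the covariate sentence does not resolve it.
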